### Measurement: process evaluation

#### Assessing parameters and feasibility for a future trial

The mixed-method process evaluation will assess variables associated with intervention implementation processes. Recommended intervention process outcomes (for implementation) include acceptability, adoption, appropriateness, feasibility, fidelity, implementation cost, penetration and sustainability [78]. In this feasibility trial, we will focus on evaluating:
Acceptability of PST-IPV and of the study design to women and health workers in terms of uptake, completion and drop-out ratesAdoption by health workersAppropriateness from women and health workers’ perspectivesFeasibility in terms of practical organisationFidelity of deliveryCostSafety

The following administrative data will be collected, which will inform the feasibility outcome measures shown in brackets:
Screening rates and reasons for refusal (acceptability)Recruitment rates (acceptability, feasibility)Numbers of eligible women at each clinical site (appropriateness)Proportions of eligible women agreeing to participate (acceptability)Willingness to be randomised and comprehension by participants of randomisation (acceptability of allocation)Session duration (appropriateness, feasibility, fidelity)Take-home activity completion (acceptability, fidelity, appropriateness)Drop-out rates (acceptability, feasibility)Follow-up rates (feasibility of retention)

Research staff will document key site features to enable comparison of process data, and keep field journals noting:
Staff willingness to participate at each site and retention in the study (acceptability, adoption, appropriateness, feasibility)Optimal recruitment procedures (feasibility)Acceptance of randomisation at each site (acceptability, appropriateness, feasibility)

#### Qualitative interviews

The acceptability and burden on women and staff of the intervention itself (including which components are experienced as helpful or unhelpful), randomisation, outcome measures and follow-up will be assessed through qualitative interviews with a purposively sampled sub-group of approximately six women (three per intervention arm) and six staff (three per intervention arm). Interviews will also explore feasibility and acceptability of the study’s SOP, which dictates the management of safety, confidentiality and ethical concerns, risk disclosures during sessions and research contacts. Interviews will be conducted in Amharic by research staff who did not have extended contact with participants during the trial in a private location convenient to them. Participants will be compensated for their time, and interviews will be audio-recorded, transcribed and translated into English.

#### Intervention fidelity and supervision

Health workers trained to deliver PST-IPV and standard PST will receive monthly supervision with a local psychiatric nurse. Health workers will audio-record PST-IPV and standard PST sessions with the participant’s consent for review by their supervisor and to inform discussions of challenging cases during supervision sessions.

A random sample of these audio recordings will be evaluated using the ENACT scale [79] to assess therapist competence (quality) alongside supervisor observations and therapist logs. ENACT has been adapted for the Ethiopian context and has been shown to be reliably administered by trained clinicians [80].

Recordings will also be evaluated for intervention fidelity and session completion using a checklist of session components. Supervision records and therapist logs will also be reviewed for intervention fidelity and contamination between arms [27]. The frequency and duration of IPV-specific content during recorded sessions of both PST-IPV and standard PST documented in therapist logs will also be noted to determine the extent to which participants raise and explore IPV-related problems during sessions. The quality of therapist–client rapport will be assessed using the Amharic-translated helping alliance questionnaire [81], which has been tested in this setting [82].

Outcome assessors will receive supervision from a Psychology Masters-qualified supervisor. Supervision logs will include discussing any items which are poorly understood or completed, and reviewing the time taken for outcome assessment to assess its acceptability and feasibility.

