### Masking

Given qualitative differences between PST and PST-IPV, clinicians delivering the intervention cannot be masked to participant allocation. To avoid contamination, PST-IPV, standard PST and enhanced usual care will be delivered by different practitioners who have either attended a PST-IPV or a standard PST training course, or received basic training to provide enhanced usual care. Post-intervention outcome assessments will be conducted by trained, independent assessors (working in separate offices from practitioners delivering interventions and not travelling together) masked to intervention allocation, with a minimum post-high school diploma level of education. Independent assessors will document any incidents of unmasking. Data analysts will also be masked to intervention allocation.

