### Intervention arms

Participants randomised to PST-IPV or standard PST will attend four intervention contacts within a maximum of 8 weeks. Where birth occurs before the end of treatment, the feasibility of continuing PST-IPV or standard PST post-natally will also be assessed.

Both manualised interventions will be delivered by trained health workers, such as nurses and midwives, supervised by Psychology Masters-level qualified research staff, with access to a project mental health professional for clinical concerns. Responses to concerns and risk incidents will follow standard operating procedures (SOPs). Government-employed health workers trained to deliver the interventions will be paid for their time.

Both PST-IPV and standard PST intervention arms follow the same structure of four sessions, based on the model successfully employed in South Africa and adapted for this rural Ethiopian setting [27, 66]. Session 1 focuses on basic psychoeducation, introduction to PST, identifying the most important things in the woman’s life and categorising problems into three groups. Session 2 focuses on revising session 1, coping strategies for ‘group A’ problems (which are upsetting but do not influence the most important things in the woman’s life) and the six-step problem solving method for ‘group C’ problems (which are important and can be solved). Session 3 focuses on revising session 2, coping strategies for ‘group B’ problems (which are important but cannot be solved) and psychoeducation about the phases of coping with bereavement and loss. Session 4 focuses on revising session 3, using problem solving skills in everyday life and reviewing how the coping strategies worked in practice. All sessions involve assigning and reviewing take-home activities.

PST-IPV content and materials are adapted to address the needs and experiences of women affected by IPV, whilst standard PST content and materials are generic. Adaptations for women experiencing IPV include training staff using content and materials from the new WHO curriculum on caring for women subjected to violence [67], attention to safety and sensitivity where women list IPV-related problems during sessions (including training with worked examples of problem solving focused on IPV), and adaptation of PST case studies to reflect common problems associated with IPV.

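### IPV content in the two PST arms is measured from therapists' own logs, which leaves the comparison open to differential recording by arm; the existing recordings are a better source

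*Protocol article*

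**What the plan says.** Under Intervention fidelity and supervision, the protocol article names the measure and its source as "The frequency and duration of IPV-specific content during recorded sessions of both PST-IPV and standard PST documented in therapist logs". The sentence goes on to say that these "will also be noted to determine the extent to which participants raise and explore IPV-related problems during sessions".

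Contamination is dealt with in the sentence before: "Supervision records and therapist logs will also be reviewed for intervention fidelity and contamination between arms".

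Recordings also exist: "Health workers will audio-record PST-IPV and standard PST sessions with the participant’s consent for review by their supervisor". A random sample is rated for therapist competence with ENACT, and "Recordings will also be evaluated for intervention fidelity and session completion using a checklist of session components".

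On who delivers the sessions, the Masking section assigns each arm to "different practitioners who have either attended a PST-IPV or a standard PST training course" (or, for enhanced usual care, to staff given basic training) and states that clinicians cannot be masked. The Intervention arms section lists, among the adaptations for women experiencing IPV, "training staff using content and materials from the new WHO curriculum on caring for women subjected to violence", "whilst standard PST content and materials are generic".

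**The concern.** A log captures what the therapist recognised and chose to write down. The stated target is something else: what participants raise and explore. The two agree across arms only if therapists in both arms recognise and record IPV content equally well. Here the therapists differ by arm, and the training said to set PST-IPV apart is training in recognising and responding to violence. Any difference in recording habits would enter the comparison as if it were a difference between the women's sessions.

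The comparison has some weight because every participant reports past-year IPV, so IPV problems can be expected in both PST arms. How much of this standard PST already takes up helps to judge how distinct PST-IPV is. The Statistical analysis section says that quantitative process data will shape the design of the future trial, including its measures against contamination. Under-logging in standard PST would make the arms look more distinct than they are.

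**Working it through.** The protocol article gives no figure for logged IPV content, so there is nothing to reproduce. The check is to read the sections together and then to illustrate the possible size.

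**Reading the sections together**

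1. Source of the measure: therapist logs, in both PST arms (Intervention fidelity and supervision).
2. Who keeps the logs: different practitioners in each arm, not masked (Masking). No therapist logs in both arms, so therapist and arm cannot be separated.
3. Whether the recorders have the same preparation: the WHO curriculum on violence appears among the PST-IPV adaptations and standard PST is described as generic (Intervention arms). That standard PST therapists do not receive this training is an inference from these two sections; the article does not say so outright.
4. Whether another source is stated to measure IPV content:
   - ENACT ratings measure competence.
   - The checklist covers session components. Both arms share the same four-session structure, so it need not separate them on IPV content, although its items are not shown.
   - Supervisors review recordings, and supervision records are reviewed for fidelity and contamination, but no count or timing of IPV content is mentioned.
   - Qualitative interviews cover about three women and three staff per intervention arm, which is too few to quantify content.

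**Illustration (all inputs assumed)**

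Logged proportion = true proportion of sessions with IPV content × probability that the therapist logs it.

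Take a true proportion of 0.50 in both arms and a logging probability of 0.90 in PST-IPV, so that PST-IPV shows 0.50 × 0.90 = 45%.

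| Logging probability in standard PST | Standard PST shows | Spurious gap |
|---|---|---|
| 0.90 | 0.50 × 0.90 = 45% | 0 points |
| 0.70 | 0.50 × 0.70 = 35% | 10 points |
| 0.50 | 0.50 × 0.50 = 25% | 20 points |

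The true difference is zero in every row. If standard PST therapists logged more fully than PST-IPV therapists, the gap would have the opposite sign. The article gives no logging rates, so it settles neither the size nor the direction.

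**The case against.** The strongest reply has five parts.

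- **Logs in both arms are meant to document IPV content.** Standard PST therapists may be prompted by the form rather than rely on unaided noticing. The form is not shown, and the article places data collection forms in a supplementary file. This stands as a reason why the effect could be small or absent. A prompt would not, however, equalise what therapists with different training count as IPV content, or for how long.
- **The logs do not stand alone.** Supervisors review recordings in both PST arms, supervision records are a named source for contamination, and interviews are triangulated with the quantitative process data. This stands as a partial offset, but none of these is stated to measure how often or for how long IPV is discussed.
- **The quoted item is not the contamination measure.** A reader might infer that the contamination check itself is biased by arm. The text does not support that: the item's stated aim is how far participants raise and explore IPV problems, and contamination is reviewed from supervision records as well as logs.
- **IPV work in standard PST is not in itself contamination.** PST works on the problems a woman brings, and all participants have experienced IPV. An IPV problem she raises and works through with generic PST is standard PST as designed. Contamination would be delivery of the adapted PST-IPV material in that arm. This stands in full.
- **The item is minor.** The objectives concern feasibility, acceptability, parameter estimation and refinement, and no decision rule or between-arm test rests on logged IPV content. This limits the importance of the point but does not make the logs a good source when recordings of the same sessions exist.

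**Conclusion.** The point holds as a risk. The log-based comparison of IPV content between PST-IPV and standard PST is open to differential recording, because the recorder is confounded with arm and the recorders differ in training relevant to the thing recorded. The illustrative gap runs from 0 to 20 percentage points under assumed logging rates; the actual size is unknown and could be zero. It would be going too far to say that the measure is biased, because the article contains no recording rates that would show it.

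The conclusion rests on two readings: that the logs are the source of the measure, which is the natural sense of the sentence, and that training on violence is confined to PST-IPV therapists. The effect is limited to a process measure. PHQ-9 comparisons, standard deviations, drop-out estimates and sample size do not depend on it.

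**What to change.** In the recordings from both PST arms that are already being rated, add items to the existing checklist for the frequency and approximate duration of IPV-specific content. Use the same rater for both arms, unaware of allocation as far as possible. Code two things separately:

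- delivery of the adapted PST-IPV material in standard PST sessions (contamination);
- IPV problems raised by the participant and handled with generic PST (not contamination).

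Base the between-arm description on these ratings. Keep the logs as a supplement and report log-versus-recording agreement by arm, which is itself a useful feasibility result for choosing the measure in the future trial.

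The cost is some extra rating time, since estimating duration means listening through the session. No new recordings or staff are needed. Two limits should be acknowledged: coverage extends only to sampled sessions with consent to recording, and a rater may recognise the arm from adapted content, so masking will be imperfect.

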### Statistical analysis

We will follow the Consolidated Standards of Reporting Trials (CONSORT) extension to randomised pilot and feasibility trials [83].

We will review process evaluation data for indications of sub-group differences in uptake, recruitment and retention of participants by site, health worker, recruitment method/site, participant (age, education level, religion, parity) and health worker characteristics (age, profession, years of experience). Quantitative scale results will be analysed using STATA [84].

Feasibility studies are not powered to calculate effect sizes but standard deviations and drop-out rates will be calculated on the intention-to-treat sample (all women who were randomised, regardless of uptake of the intervention) to inform sample size calculation for a future RCT, for outcome measures, recruitment rates and drop-out rates. Quantitative process data will determine future RCT design improvements, such as session number and duration, recruitment, outcome measures, and strategies preventing contamination. The extent of missing data will be evaluated as part of the process evaluation. For clinical outcome measures, missing data will not be imputed. Rather, standard deviations will be calculated using data from participants for whom outcome measures are available.

We will apply the framework approach to thematic analysis of qualitative interviews [85] and triangulate the results with quantitative process data through researcher meetings. The full descriptive analysis will include contextual barriers and facilitators influencing study outcomes.

### Ethical considerations

Strategies to ensure data protection, quality assurance and dissemination of results are outlined in Supplementary file 3 and data collection forms are provided in Supplementary file 4. Ethical approval has been provided by the Institutional Review Board of the College of Health Sciences, Addis Ababa University, Ethiopia (protocol number: 032/19/CDT) and the Psychiatry, Nursing & Midwifery subcommittee of King’s College London’s College Research Ethics Committee, UK (reference: HR-18/19–9230); see Supplementary file 5.

This study involves recruitment of potentially vulnerable women, disclosure of IPV, and detecting depression, anxiety and PTSD symptoms. The SOP therefore outlines actions to mitigate potential risks. If participants disclose current exposure to IPV, research staff will be trained to listen non-judgementally, offer privacy and confidentiality, and information about local agencies who can provide assistance (see Supplementary file 2) [42] in keeping with WHO guidelines, irrespective of the study arm.

#### Sensitivity

Female research staff will be carefully selected with the sensitivity of subject matter in mind. Once recruited, they will receive locally tailored IPV training [44]. When approaching women, great sensitivity will be exercised. In all cases, care will be taken to ensure that women do not feel pressurised to participate. We will ensure anonymity of interview transcripts and any quotations used in publications or reports.

#### Safety

The SOP outlines measures to mitigate potential risks to participants, including abusive partners learning of their involvement. These include a protocol for responding to concerns or disclosures of risk, emergency contact information, conduct when communicating with vulnerable participants, documenting and responding to serious adverse events and reporting them to the King’s College London and Addis Ababa University institutional review boards which have provided ethical approval for this trial. Numbers of serious adverse events will be calculated per trial arm. A data monitoring committee will not be instituted due to the small sample size of this feasibility trial, which is not powered for interim analyses.

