Participants randomised to PST-IPV or standard PST will attend a total of six contacts: one baseline pre-intervention research assessment, four intervention contacts and a follow-up research assessment contact 9 weeks after recruitment. The feasibility of follow-up 9 weeks after recruitment will be assessed and may change, depending on gestation of pregnancy at the time of enrolment.

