### Enhanced usual care arm

One-third of participants will be randomised to information only about sources of support (enhanced usual care; see Supplementary file 2). They will attend two contacts: one pre-intervention assessment at which they are provided with information about relevant sources of support, and one follow-up assessment 9 weeks later.

In our meta-analysis we found that randomisation of control group participants with depression, anxiety, PTSD or psychological distress symptoms and IPV exposure to waiting list, treatment as usual, or enhanced usual care arms is widespread [21]. This, coupled with the lack of any standard intervention provision for perinatal depression and/or IPV in rural Ethiopia and the provision of safeguards in the study design, justify the use of a control arm, which comprises enhanced usual care (provision of information about sources of support).

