Post-traumatic stress symptoms using the PTSD checklist for the Diagnostic and Statistical Manual version 5 (PCL-5) [68] which has been adapted for a rural Ethiopian contextAnxiety symptoms using the Generalised Anxiety Disorder 7 (GAD-7) scale [69]Disability using the 12-item Ethiopian adaptation [70] of the WHO Disability Assessment Schedule (WHODAS 2.0) [71]IPV: participants will be asked about past-month IPV at baseline and 9-week follow-up to determine whether the frequency of different types of IPV (physical, sexual, psychological, coercive control) change during the study periodSelf-efficacy using an adapted self-efficacy scale validated in Ethiopia for sexual health research [72]Mastery (the extent to which the person considers themselves in control of forces affecting their lives in important ways [73]) using a 15-item multi-cultural mastery scale [74] adapted for rural, non-Western communitiesPerceived social support using the Oslo Social Support Scale 3 (OSSS-3) [75] previously used in this region in a study of antenatal depressive symptoms [46]Health care-seeking behaviour using the client service receipt inventory [76] adapted for Ethiopia [77] and modified to focus on the past month; the client service receipt inventory will be used to quantify the frequency of primary health care visits, inpatient admissions, private sector (including traditional healer) contacts, medications and investigations of women in each arm, in the past month, pre- and post-participationAdverse events or unanticipated harms taking place during the study periodObstetric and neonatal outcomes: HEWs, who maintain maternal care records, will report the location of birth and any stillbirths and early neonatal deaths among study participants, attendance at subsequent ANC appointments and medication prescriptions for physical and mental health, as they are not reliably self-reported [47]; where women attend ANC at a combination of HEW health posts, health centres and/or primary hospitals, antenatal contacts at all relevant services will be collected; the feasibility of collecting this data will be explored during analysisAttitudes towards gender roles using the WHO Attitudes Towards Gender Roles questionnaire [42]

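### The per-arm count of serious adverse events may be inflated in both PST arms relative to enhanced usual care, because it is not limited to sources common to all arms

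*Protocol article*

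**What the plan says.** - **Serious events.** Ethical considerations, Safety: "Numbers of serious adverse events will be calculated per trial arm". The sentence gives no source or period for the count. Documentation of these events is left to a standard operating procedure (SOP) that is not shown.
- **Contacts in the PST arms.** Intervention arms: "Participants randomised to PST-IPV or standard PST will attend a total of six contacts". The sessions fall in the treatment window: participants "will attend four intervention contacts within a maximum of 8 weeks".
- **Contacts in enhanced usual care.** Enhanced usual care arm: "They will attend two contacts: one pre-intervention assessment", the other being the 9-week follow-up.
- **Harms as an outcome.** Secondary participant outcomes lists adverse events over the whole study among the measures taken at baseline and 9 weeks in every arm. Masking makes the post-intervention assessors independent and masked. Health extension workers (HEWs) report stillbirths and early neonatal deaths for all participants.
- **IPV.** Secondary participant outcomes: "participants will be asked about past-month IPV at baseline and 9-week follow-up". The stated purpose is to see whether the frequency of IPV changes over the study.

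**The concern.** A count of events per arm compares arms fairly only if an event has a similar chance of being recorded in each. Women in the PST arms meet a trained clinician four times between baseline and follow-up. The article describes audio recordings, therapist logs and supervision for those sessions and describes nothing equivalent for enhanced usual care. According to Qualitative interviews, the SOP manages risk disclosures during sessions as well as during research contacts. According to Safety, the same SOP covers the documenting of serious adverse events. An event disclosed in a session can therefore plausibly enter the per-arm count, whereas the same event in enhanced usual care would have to surface at week 9 or through routine care.

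Safety is one of the named topics of the process evaluation, no data monitoring committee is planned, and the per-arm count is the only comparative summary of serious events that the article states. With 25 women per arm, one or two events recorded only because of extra contact could colour the safety reading that goes forward to a full trial.

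**Working it through.** **1. Contacts (the plan's own figures).** PST-IPV and standard PST: 1 baseline + 4 sessions + 1 follow-up = 6, which reproduces the stated six. Enhanced usual care: 1 + 1 = 2, as stated. After baseline: 5 against 1. PST-IPV against standard PST: 5 against 5, so contact number cannot separate those two arms.

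**2. How far unequal contact could move the count.** Assume equal true risk in all arms, and let

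- f = share of women followed up at week 9,
- s = sensitivity of the 9-week adverse-event question,
- c = chance that an event is picked up at any one session after it occurs,
- k = sessions remaining after the event, set at 2 of the 4.

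Share detected in enhanced usual care = f·s. Share detected in a PST arm = 1 − (1 − f·s)(1 − c)^k. The formula treats the detection chances as independent and lets women lost at week 9 still be detected in sessions. No document gives s, c or k, so they are varied: s from 0.5 to 1.0 and c from 0 to 0.6. For f, 1.0 and 0.7 are used; the latter borrows the 30% drop-out figure in Participant sample size. Expected counts below use an assumed true risk of 10% and 25 women per arm.

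| f | s | c | Enhanced usual care | PST arm | Ratio |
|---|---|---|---|---|---|
| 1.0 | 1.0 | 0.6 | 2.50 | 2.50 | 1.00 |
| 1.0 | 0.8 | 0.6 | 2.00 | 2.42 | 1.21 |
| 1.0 | 0.5 | 0.6 | 1.25 | 2.30 | 1.84 |
| 0.7 | 1.0 | 0.3 | 1.75 | 2.13 | 1.22 |
| 0.7 | 0.8 | 0.3 | 1.40 | 1.96 | 1.40 |
| 0.7 | 0.5 | 0.6 | 0.88 | 2.24 | 2.56 |

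Worked extreme: f·s = 0.7 × 0.5 = 0.35; PST arm 1 − 0.65 × 0.4² = 0.896; 0.896/0.35 = 2.56. The ratio does not depend on the assumed 10%.

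The ratio is 1.00 whenever c = 0, and also when follow-up is full and the 9-week question misses nothing. Under equal true risk and equal follow-up it never falls below 1.00, so the direction is fixed even though the size is not.

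**3. Comparison on common sources only.** Leaving session-detected events out of the comparison sets c = 0. The expected ratio is then 1.00, given equal follow-up.

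**4. Coverage of the IPV item.** Nine weeks = 63 days. A month of 28 to 31 days covers 28/63 = 44% to 31/63 = 49%. That leaves 32 to 35 days (51–56%) unasked, in every arm alike. Sessions may run from enrolment to week 8, so the unasked days include the early part of treatment.

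**The case against.** The strongest reply is that the plan already has a suitable measure: a whole-period adverse-event outcome, taken in all arms at the masked 9-week assessment, plus HEW records kept whatever the arm. The SOP and data collection forms, which are not shown, may also fix the source and period of serious-event capture. Women in enhanced usual care stay in antenatal care and in touch with HEWs, so their events are not invisible. The plan states a count and no test of serious events, and no progression decision is tied to it.

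Much of this stands. A reader might infer that comparisons of harm are biased outright. The documents support only that they may be: nothing shows that session disclosures are counted, and a complete 9-week question with full follow-up would remove the effect. What survives is that the Safety sentence does not tie the per-arm count to the common sources. The HEW items named in the article do not include violence or self-harm.

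Two other inferences fail.

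- A reader might think PST-IPV will look worse than standard PST because it is asked about more. Contacts are equal, no harm questions are scheduled at sessions in either arm, and IPV content is noted in sessions of both. The violence-specific training of PST-IPV staff might raise detection, but nothing in the article puts a size on that.
- A reader might take the past-month IPV window as a biased comparison. It is identical across arms and visits, which is sound for comparing follow-up with baseline. Its fault is incomplete coverage.

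Restricting the comparison to the 9-week interview alone would also be wrong. It would drop women who died, were too ill or were lost, and they may carry the most serious events.

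**Conclusion.** The point holds in a limited form. The per-arm count of serious adverse events may be inflated in both PST arms relative to enhanced usual care, because there are five post-baseline study contacts against one and the count is not confined to sources that all arms share. The illustrated inflation runs from none to 1.84-fold with full follow-up, and from none to 2.56-fold with 30% loss. At the assumed 10% risk, the extreme is about 2.2 against 0.9 events per 25 women. Those sizes rest on assumed detection rates and on session-detected events entering the count, which the article makes plausible but does not state.

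The IPV item is a separate and smaller matter. It is fair between arms, but it asks about less than half of the period over which it is meant to show change. The 44–49% assumes follow-up at exactly nine weeks, which the plan says may shift with gestation at enrolment.

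**What to change.** 1. Keep the full all-source count of serious adverse events per arm.
2. Beside it, tabulate events by source of detection: the 9-week interview, HEW records, sessions, and other contacts.
3. State that the between-arm reading of harms rests on the sources common to all arms, namely the masked 9-week adverse-event question covering the whole study and HEW records. Show session-detected events separately.
4. Report the number not followed up in each arm, since a common-source comparison is fair only if follow-up is similar.
5. Keep the past-month IPV item at both visits for comparability with baseline. Optionally add one item at week 9 on any IPV since enrolment, which would bring coverage to all 63 days in every arm.

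The cost is one extra table and, if the item is adopted, a short addition to an interview that the plan wants to keep within an hour. How events are acted on and reported to the ethics boards does not change. If the SOP already fixes the source and period, a sentence saying so would meet part of step 3.
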